**2. Background**

**A. HIV/AIDS, HSV-2, and high-risk behaviors among adolescent females in Zimbabwe**

Zimbabwe has one of the highest HIV infection rates worldwide, at an estimated 30% [6]. Zimbabwe’s HIV epidemic has a disproportionate impact on adolescent girls. Approximately 25% of Zimbabwean females aged 15-24 are infected with HIV, compared to 11% of like-aged males [8]. HSV-2 prevalence levels of up to 45% have been found among females aged 15-19, making it the most prevalent STI among Zimbabwean women under 20 years of age [9, 10]. Fifteen percent of girls in Zimbabwe have begun childbearing by age 19 [12].

B. HSV-2 as an indicator of sexual risk behavior and relevance to HIV transmission

The prevalence of genital herpes virus, type 2 (HSV-2) infection as measured by antibody to HSV-2 is considered an excellent objective indicator of sexual risk behaviors [5]. Serologic surveys of HSV-2 antibody have shown that persons with high-risk profiles, such as STD patients and female sex workers, have very high HSV-2 prevalence; and persons with low risk profiles have low or zero HSV-2 prevalence [5]. In addition, HSV-2 is considered the most important facilitating factor for HIV transmission in developing countries [13-15] most likely because HSV-2 is the major STI associated with genital lesions, which are known to increase thetransmissibility ofHIV [9, 10, 16-19].

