**2. Pilot Study Design**

We conducted a cross-sectional study among 200 in and out of school girls between 16 and 19 years of age living in our research sites. Convenience sampling was used to recruit participants into the study. Participants were enrolled at clinic locations in both sites, as well as through a mobile clinic facility. A subset of 50 orphans (defined as having lost at least one parent) was enrolled into the pilot intervention and was followed up at 3 and 6months.

Information at baseline and follow-up visits was collected from study participants using both quantitative and qualitative methods of data. Quantitative surveys, using face to face interviews and ACASI, were conducted at baseline, and at 3 and 6 months to collect information on demographics, HIV and RH knowledge, sexual behavior and contraceptive use, partners, relationship power and current economic activities. Biological specimens for HIV, HSV-2 and pregnancy were collected and tested. Qualitative data was collected through observation and in-depth interviews throughout the pilot to provide information on implementation quality and to assess successes and failures of the intervention. Process evaluation data on training attendance, loan disbursement, loan repayment, and business assessments were also collected. The main outcome variables assessed were socio-demographic characteristics, sexual behavior, control over sexual interactions, sexual and physical abuse, participation in and knowledge gained from training, micro-enterprise activities, including income generation, and HIV, HSV-2, and pregnancy status.

3. Findings

The pilot study cross sectional survey (n=200) showed that orphans and out of school girls were more likely to be sexually active (40% vs 24%), have a higher prevalence of HIV (9% vs 3%), HSV-2 (10% vs 6%) and to have had a past or current pregnancy (15% vs 5%). Among the 50 enrolled in the pilot intervention, 43% had ever had sex, 57% and 14% had ever used male and female condoms respectively and 14% had ever been raped. Fifty seven percent had been sexually active in the last three months and 44% received basic needs/money from primary sexual partner at baseline.

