**4. Methods**

**A. General Study Design**

We propose a randomized controlled trial of an intervention combining a vocational training package -- including a conditional stipend and completion bonus -- with life-skills education and social support, compared to life-skills education alone. The study will begin with six months of start-up activities, and enrollment will take place within a six-month period at the beginning of the study. The economic livelihood intervention and life-skills programs will be administered for one year and participants will be followed for one year post-intervention. Data collection and service provision to participants will be provided through a health clinic and occasional visits using a mobile clinic. The frequency of intervention visits (i.e. visits related to the intervention program such as life-skills training, SHAZ reunions, and vocational training) is described below. Visits for data collection, including biological and behavioral outcome data, will be collected at baseline, and every six months thereafter for a total of five visits over the three year period. We will follow participants for one year after the intervention to ensure sufficient power to examine our primary outcome (Aim 1) as well as to establish the temporal association between the intermediary effects of increased economic opportunity and improved sexual negotiation skills in enhancing participants’ control over sexual interactions (Aim 3). Finally one year of follow-up will allow us to assess the intervention’s sustained effects on high-risk behavior (Aim 2). (Please see appendices: Intervention Design and Study Design Flow Chart)

**Prevention for Positives component:** The SHAZ main study has completed its enrollment for the ongoing intervention study, with a total of n=315. In order to assess the feasibility of implementing this intervention with HIV and HSV-2 positive clients, we will enroll an additional cohort of n=50 according to the same criteria as was used in the main study, except that those who are HIV and/or HSV-2 positive also will be eligible to enroll.

In order to meet this objective, we will contact and invite all participants who screened out of the study because of positive results (n=40) and invite these to re-screen for the study. We will then continue to recruit additional participants until we meet the desired sample size n=50.

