#### Methods of Data Analysis

**1.a. Sample Size – Quantitative**

Sample size calculations for Aim 1 assume that the background annual incidence rate for HSV-2 is 16% (corresponding to a prevalence rate following two years of follow-up of approximately 22%), and that participants will be followed for three years. Further, we conservatively assume that 20% of participants will be lost to follow-up (our average loss to follow-up over all completed studies is 12% [C.1]). Although individuals will form the unit of randomization, the fact that they will be associated via membership in life skills cohorts may induce correlation between individual outcomes within groups (assumed to include an average number of 25 girls) –We account for this using methods described in Hayes and Bennett [77], which take into account both the number of individuals randomized into each arm and the between-group variation in incidence rates induced by within-group correlation in infection outcomes. Incidence rates will be compared between arms using a two-sample t statistic adjusted to account for this source of variation. The corresponding coefficient of variation is assumed to be 0.2, a conservative estimate similar to values used in other studies [77, 78]. With these assumptions, our proposed sample size **of 300 (150** individuals randomized to each arm) will provide 80% power to detect a relative reduction in HSV-2 incidence as small as .53 at the 5% significance level. This corresponds to a 47% reduction in HSV-2 incidence (from 12% to 6.3%). Because unintended pregnancy is expected to have similar, if not higher incidence rates, the above calculations apply to this outcome as well.

Similar calculations for the HIV infection outcome (at 8% prevalence) indicate that we should have 80% power to detect a relative risk comparing incidence in the intervention group to the control group as small as .29 at the 5% significance level. This corresponds to a 70% absolute reduction in HIV incidence, assuming a background annual HIV incidence rate in the target communities of approximately 4%. This is an effect we do not expect to be able to detect given our sample size. We will, however, be able to report trends. The high prevalence rates cited in section B.1. were among young females in an antenatal clinic who were obviously sexually active and practicing unprotected sex. Among adolescents in Zimbabwe, HSV-2 rates tend to be three to five time higher than HIV rates [10].

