**D. Subject Recruitment – Main Study**

**1. Sources:** In Zimbabwe, orphans and their families are eligible for funds collected through a countrywide AIDS tax paid by private citizens and businesses***.*** To distribute the funds, which are delivered on a monthly basis, each District AIDS Action Committee (DAAC)has developed and maintains a list of orphans, their ages and addresses through annual door-to-door and street-based enumeration. The DAAC under which Chitungwiza falls has agreed to assist us in recruiting orphans by referring them from their lists, while maintaining the confidentiality of the potential participants We will also be recruiting participants from community based venues such as market places and youth halls.

**2. Initial contact method:** During their monthly visits, DAAC members will describe the study to potential participants and invite those interested to contact us via visits to the clinics, email, telephone or project offices. When potential participants contact us, study staff will provide additional information about the study and will determine their eligibility. Participants recruited by study staff members will similarly be invited to visit the clinics and be screened for eligibility.

3. **Prevention for Positives cohort**: Approximately 40 participants screened for the main study were positive for HIV and/or HSV-2 and therefore not eligible. We will contact these 40 participants and invite them to re-screen for the study. If they are still eligible for the study for all other criteria, they will be invited to enroll. We will continue to recruit participants using procedures already described and approved (D, 1 and 2 above) until the desired sample size of 50 is reached. In this way stigma associated with being part of a new “positive” cohort will be avoided as the additional participants enrolled to meet our sample size will include both positive and negatives. No language or recruitment methods (flyers, outreach) will be employed that imply the new cohort is a “positive cohort’, nor single out any participant as positive throughout the process, and no changes will be made to recruitment documents. Additionally, the Chitunguiza CAB who is very supportive of Shaz, will be kept updated and involved from the beginning and will help manage any rumour or related misconceptions.

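### The assumed HSV-2 incidence (16%, then 12% a year) is never reconciled with the protocol's own lower pilot and screening prevalences, and the stated 80% power does not hold over any plausible range

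*Protocol*

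**What the plan says.** Section 1.a, Sample Size – Quantitative, opens with "Sample size calculations for Aim 1 assume that the background annual incidence rate for HSV-2 is 16" per cent, described as "corresponding to a prevalence rate following two years of follow-up of approximately 22" per cent. It takes three years of follow-up, 20% loss, groups of 25 girls and a between-group coefficient of variation of 0.2. It concludes that 150 girls per arm give 80% power at a rate ratio of 0.53, expressed as a fall from 12% to 6.3%. Pregnancy is covered by one sentence: "Because unintended pregnancy is expected to have similar, if not higher incidence rates, the above calculations apply to this outcome as well".

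Other sections give figures for the girls the trial recruits:

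- The pilot findings (Background, part H), for orphans and out-of-school girls against the others: "HSV-2 (10% vs 6%) and to have had a past or current pregnancy (15% vs 5" per cent). In the same group 9% had HIV and 40% were sexually active.
- Section D, Subject Recruitment: "Approximately 40 participants screened for the main study were positive for HIV and/or HSV-2 and therefore not eligible".
- Section 4.A, General Study Design: main-study enrolment is complete, "with a total of n=315". The same section describes one year of intervention and one year of follow-up after it.
- Background, part A, for the country as a whole: "Fifteen percent of girls in Zimbabwe have begun childbearing by age 19".

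The sample size section does not mention the pilot prevalences or the screening result.

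**The concern.** A prevalence at ages 16-19 accumulates all past infections. A group in which about one girl in ten is infected, after whatever exposure she has had, is hard to square with 12-16% of uninfected girls becoming infected each year. Events drive power here, and expected events scale directly with incidence. The protocol admits that it is underpowered for HIV but claims 80% for both primary outcomes. If the true rate is well below the assumed one, a null result would say little about whether the intervention works, and the stated power would lead readers to take it as evidence of no effect.

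**Working it through.** **Method.** The protocol names the Hayes and Bennett method, so I use its rate formula with c groups per arm, y person-years per group, control rate λ0, λ1 = 0.53 λ0 and coefficient of variation k:

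power = Φ( √[ (c − 1)(λ0 − λ1)² / { (λ0 + λ1)/y + k²(λ0² + λ1²) } ] − 1.96 )

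Inputs from the protocol: c = 150/25 = 6; k = 0.2; y = 25 × 0.8 × years, which is 40 for two years and 60 for three. The protocol does not say whether the 5% level is one- or two-sided; I assume two-sided.

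**1. The protocol's own figure.** With λ0 = 0.12, λ1 = 0.0636, y = 60:

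- (λ0 + λ1)/y = 0.00306; k²(λ0² + λ1²) = 0.00074; (λ0 − λ1)² = 0.00318
- √(5 × 0.00318/0.00380) = 2.05; power = Φ(0.09) = 53%

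At 16% a year the result is 63%. Using c in place of c − 1 gives 61% and 71%. On a two-sided test, 80% at 0.53 appears only when stated adjustments are dropped: for example 12%, three years, no loss, no clustering and c in place of c − 1 gives 79.7%. A one-sided test at 16% with loss and clustering, again with c, gives 80.6%, but 0.53 would then mean 16% to 8.5%, not 12% to 6.3%.

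The two rates also disagree with each other. Two years at 12% gives 1 − e^(−0.24) = 21% or 1 − 0.88² = 23%, which fits the stated 22%. Two years at 16% gives 27-29%.

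**2. From prevalence to incidence.** Rate = −ln(1 − prevalence)/years at risk. The protocol does not give the years at risk, so I take 1 to 3 as an assumption.

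| Source | Prevalence | 1 year | 2 years | 3 years |
|---|---|---|---|---|
| Pilot HSV-2 | 10% | 10.5% | 5.3% | 3.5% |
| Screening, HIV and/or HSV-2 | 40/355 = 11.3% at most | 12.0% | 6.0% | 4.0% |
| Pilot, ever pregnant | 15% | 16.3% | 8.1% | 5.4% |

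The screening figure is a ceiling: at least 315 + 40 = 355 girls were screened, and HSV-2 alone cannot exceed the combined figure. For the pilot's 10% to fit 12% or 16% a year, mean time at risk would have to be only 0.88 or 0.66 years (0.105/0.12, 0.105/0.16).

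**3. Power at these rates, rate ratio 0.53.**

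| Control rate per year | Power, 2 years | Power, 3 years | Rate ratio detectable at 80%, 2 years | Same, 3 years |
|---|---|---|---|---|
| 3.5% | 16% | 22% | none | 0.07 |
| 4% | 18% | 24% | none | 0.11 |
| 6% | 24% | 33% | 0.11 | 0.22 |
| 8% | 30% | 41% | 0.19 | 0.30 |
| 10.5% | 37% | 49% | 0.27 | 0.36 |
| 12% | 41% | 53% | 0.30 | 0.39 |
| 16% | 50% | 63% | 0.36 | 0.44 |

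Detectable ratios below about 0.2 rest on so few events that the normal approximation is poor. They mean only that no realistic effect is detectable.

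**4. Events, like for like.** Expected control infections over two years are 120 × 2 × rate: about 8 at 3.5%, 25 at 10.5%, 29 at 12% and 38 at 16%.

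**5. Pregnancy.** The same formula over two years gives about 23% power at 5.4% a year and 50% at 16.3%. These rates count all pregnancies, so they are upper bounds for unintended ones.

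**The case against.** The strongest reply is that nothing in the protocol measures incidence. The pilot and screening data are prevalences, and any rate drawn from them depends on an exposure time that is not reported. Several further points stand:

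- Only 40% of the pilot group were sexually active. As others start, incidence in an ageing cohort may exceed the past average.
- The pilot was a convenience sample and the subgroup size is not given. If it were 100, the 95% interval for 10% would be about 6-17%. The group may also combine girls who were orphans with girls who were out of school, while the trial requires both.
- The assumed rate has a derivation inside the protocol: 4% annual HIV incidence times a three- to five-fold HSV-2 to HIV ratio gives 12-20%. The background also cites HSV-2 prevalence of up to 45% at ages 15-19.
- For pregnancy, the pilot ordering (15% against 10%) agrees with a rate similar to or higher than HSV-2.

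The counter-evidence has limits. The sample size section itself says that the high background rates came from antenatal attenders. The pilot's HSV-2 to HIV ratio was 10:9, and the reference given for the larger ratio is listed as a study in rural Tanzania. The pregnancy ordering supports the comparison with HSV-2 but does not supply a rate of 12-16%.

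A reader might go further and infer that the protocol's data contradict the assumption and fix HSV-2 incidence at 4-5% a year, with power near 20-25%. One route is to take 9% HIV prevalence and 4% HIV incidence, infer −ln(0.91)/0.04 = 2.4 years at risk, and obtain 0.105/2.4, about 4.5%. That mixes an assumed incidence with pilot prevalences and needs a constant hazard. The documents do not support a single value.

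**Conclusion.** The point holds as an unreconciled tension, not as a refutation. The pilot's 10% suggests HSV-2 incidence of roughly 3.5-10.5% a year, against 12-16% assumed. Power at 0.53 is then about 16-37% over the two-year design, or 22-49% over the three years used in the calculation. Part of the shortfall has nothing to do with incidence: at 12-16% power is already only 41-50% over two years and 53-63% over three.

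For pregnancy the evidence is weaker. The pilot is compatible with roughly 5-16% a year for all pregnancies. What can be said is that the protocol gives no rate for unintended pregnancy and so has no basis for applying the HSV-2 calculation to it.

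The result rests on 1-3 years at risk, a roughly constant hazard, a two-sided test, and the protocol's own loss, group size and coefficient of variation. No rate from 3.5% to 16% gives the stated 80% under these inputs.

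**What to change.** In section 1.a, replace the single 80% statement with a table of power and detectable rate ratio over a range of control incidence (for example 4%, 6%, 8%, 12% and 16%), at the follow-up length that participants will actually have. Use one HSV-2 rate consistently wherever a single rate is quoted.

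Give the table separately for HSV-2 and for unintended pregnancy. Remove the sentence that carries the HSV-2 calculation over to pregnancy unless a pregnancy rate and its source are stated.

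Inform the range with the pooled, arm-blind incidence observed so far. This should be obtainable: enrolment is complete, and the Risks section says that seroconversions have already occurred. If the rate ratio were 0.53, the pooled rate would be about (1 + 0.53)/2 = 0.765 of the control rate, so the control rate lies between the pooled rate (no effect) and the pooled rate divided by 0.765.

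The cost is one blinded tabulation and a less favourable stated power. Enrolment does not change.

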**Economic Opportunity for Zimbabwean Adolescent Orphans**

1. **Study Aims**

The overall aim of this project is to determine, using a randomized controlled design, whether a economic livelihood (in this case vocational training package including monthly fees, a modest stipend based on progression and performance in the training program, and a completion bonus) and life-skills intervention, designed to increase control over sexual interactions, prevents the adverse consequences of unprotected sex among out-of-school female orphans aged 16-19 in Zimbabwe compared with a life-skills intervention alone.

**Aim 1: To assess the effectiveness of a combined vocational training package and life-skills education intervention in reducing the incidence of our primary outcomes: Herpes simplex virustype 2 (HSV2) and unintended pregnancy.** Although not powered to assess HIV as an outcome, we will nevertheless monitor HIV incidence between groups. (Note that rates of bacterial STDs are too low to consider.) We hypothesize that compared to those in the control group, adolescent female orphans receiving the combined intervention will experience a lower incidence of these outcomes.

Aim 2: To assess the effectiveness of a combined vocational training package and life-skills education intervention in reducing our secondary outcomes: high-risk behaviors (e.g., unprotected sex, number of partners, transactional sex, early sexual debut, sexual coercion and violence). Our hypothesis is identical to that for Aim 1.

**Aim 3. To examine the intermediary effects of increased economic opportunity, social support, and improved sexual negotiation skills in enhancing participants’ control over sexual interactions.** We hypothesize that the combined intervention will enable participants to, for example, increase and gain control over their income and future income-earning potential (through the vocational training intervention), thereby empowering them to use the sexual negotiating skills gained through the life-skills intervention. Together, these outcomes will increase participants’ control over sexual activity, and reduce the prevalence of sexual risk behaviors and the incidence of both HSV-2 and unintended pregnancies. This aim will allow us to examine why the intervention is or is not effective. Furthermore, if the predictive value of these outcomes is high, this may obviate the need for collection of biological data and self-reports of sensitive behaviors in future studies.

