**G. Life-skills Education and Reproductive Health**

Life-skills Education programs, also called Skills-Based Health Education, have been used for a variety of education and prevention programs, particularly sexual and reproductive health including training in sexual negotiation skills. These programs go beyond the traditional didactic information sessions, by adopting gender-sensitive, interactive, participatory methods that not only inform, but also help change attitudes and behaviors[53]. A review by UNICEF found that educational efforts with a life-skills approach were effective in behavior change. Stepping Stones, one of the curricula upon which the SHAZ! lifeskills training is based, has been implemented in a variety of cultural settings and age groups, including adolescents in sub-Saharan Africa [54]. The UNICEF report found that the Stepping Stones Program resulted in a decreased number of sexual partners, and more use of condoms among attendees [55]. That said, these evaluations occurred immediately after program implementation and there are no data on sustained change. In fact, researchers have concluded that only providing HIV/reproductive health education is a first, but inadequate, approach to sustainable behavior change [57, 58].

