- Utilize UZ-UCSF Programme referral protocols for positive study participants to facilitate access to national treatment services.
- Modify data collection tools to assess additional clinicial, behavioral, social and biological outcomes as appropriate.
- Incorporate ‘living positively’ tenants to all participants at Shaz reunions. Examples might include urban gardens and nutrition tips, etc.
- Adding qualitative interviews (and observations of Lifeskills sessions) among both control and interview participants (5 interviews each group, randomly selected, repeated over time) within the new cohort to assess issues such as group dynamics during, especially disclosure, stigma/discrimination and confidentiality.

Outcome measures to be added include:

- Clinical assessment of HIV related opportunistic infections including weight gain/loss
- CD4 counts to assess disease progression and need for referrals for treatment (CDV<250)
- Measures of disclosure, social support, experience of stigma or marginalization at home and in the community through supplemental questionnaires administrated during counseling sessions, qualitative interviews and observations of life skills sessions.

As the intervention and control trainings are designed for an initial group of 25 participants, a training session will begin each time that number of participants is achieved in a given arm. The intervention, which will be delivered in the first year of the study, will consist of five main components: 1) Life Skills education (UZ-UCSF) and basic home-based health care training (Red Cross) (intervention and control arm) 2) Guardian support 3) Choice of vocational training options as determined appropriate and available by SHAZ! guidance counselors (plus stipend/bonus, intervention only); 4) Guidance counseling for social support (intervention arm only) 5) Ongoing SHAZ reunions. There will be one year of follow-up during which time the reunions and study visits will be on-going every six months. (See intervention overview for details).

B. Overview of Intervention

i. Intervention Group

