To ensure high follow-up rates, at the completion of the participants life skills and health training sessions, intervention and control participants will participate in a graduation ceremony, and then will meet together again in SHAZ reunions every six months, identical to the intervention participants. They will not have access to guidance counseling or vocational training, but will be followed-up for the same amount of time at the same intervals as the intervention participants. Every participant will be provided with condoms and hormonal contraception if requested, and screening and treatment for symptomatic STIs. Referrals for health care will be provided on an as needed basis. Life-skills facilitators/mentors will continue to meet with their peer support groups on a monthly basis for the remainder of the study.

At the end of the study, all control participants who completed a final study visit will be offered the same vocational training that was offered to the intervention participants. The study will cover the fees of the vocational training program for 6 months, but will not provide the transport reimbursement or bonus, or the supportive guidance counseling.

**2. Time:** It will take approximately 15 minutes to explain the study and approximately 30 minutes to get informed consent. The screening interview will take 15 minutes, while the baseline and follow-up interviews will be limited to 30-45 minutes. HIV pre-test counseling will take about 30 minutes, and the time for post-test counseling will depend on the participant’s needs. Blood and urine specimen collection will take ten minutes. Pregnancy counseling will take five to ten minutes.

**3. Study Sites:** Study visits will take place in a family health clinic in Chitungwiza, an urban site-outside of Harare, Zimbabwe.

**G. R**isks/Discomforts

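### The Aim 1 power takes a background incidence as its reference rate and allows nothing for the active package that controls receive, so the stated 80% is optimistic

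*Protocol*

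**What the plan says.** The objective in Study Aims is the combined package "compared with a life-skills intervention alone".

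Section 1.a, Sample Size – Quantitative, builds Aim 1 on this premise: "Sample size calculations for Aim 1 assume that the background annual incidence rate for HSV-2 is 16" per cent, "corresponding to a prevalence rate following two years of follow-up of approximately 22" per cent. It then reports 80% power for a ratio of 0.53 and expresses this as a fall from 12% to 6.3%. The parallel HIV calculation defines its ratio as intervention against control and gives the reference rate as "assuming a background annual HIV incidence rate in the target communities of approximately 4" per cent. No separate rate for the life-skills arm appears anywhere.

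Pregnancy, the other primary outcome, inherits the calculation: "Because unintended pregnancy is expected to have similar, if not higher incidence rates, the above calculations apply to this outcome as well".

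Under F. Procedures, the shared components include "Life Skills education (UZ-UCSF) and basic home-based health care training (Red Cross) (intervention and control arm"), and "Every participant will be provided with condoms and hormonal contraception if requested, and screening and treatment for symptomatic STIs". Controls also have the same six-monthly biological testing, the reunions and monthly peer groups. Background section G says of one source curriculum for the life-skills course that "the Stepping Stones Program resulted in a decreased number of sexual partners, and more use of condoms among attendees".

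**The concern.** The ratio to be tested is combined package against life-skills arm, so the rate that drives power is the incidence in the life-skills arm. The sizing supplies a background incidence instead. The protocol itself credits a source curriculum with changing the behaviours through which HSV-2 is acquired, then sizes as if the shared package had no effect on the control rate.

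Any real effect of that package means fewer events and less power at the same ratio. Pregnancy is the plainest case, because contraception is offered on request to both arms while the expected incidence is simply described as similar or higher.

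What is at stake is mainly interpretation. A null result would be read against a stated 80% power that was available only if controls stayed at the full background rate.

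**Working it through.** **Inputs (section 1.a unless noted).** Annual HSV-2 incidence 16%; ratio 0.53; 150 per arm in groups of 25, so c = 6 groups per arm; loss 20%; three years of follow-up; between-group coefficient of variation k = 0.2; 5% level, sidedness not stated. Person-years per group: y = 25 × 0.8 × 3 = 60.

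**Formula** (the cited Hayes and Bennett method, solved for power): power = Φ( (λ0 − λ1) / SE − z ), with SE = √{ [ (λ0 + λ1)/y + k²(λ0² + λ1²) ] / (c − a) }. Here a = 0, or a = 1 for the small-cluster correction; z = 1.645 one-sided or 1.960 two-sided.

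**Step 1: reproduce the stated 80%.** λ0 = 0.16 and λ1 = 0.53 × 0.16 = 0.0848.
- (λ0 + λ1)/y = 0.2448/60 = 0.00408.
- k²(λ0² + λ1²) = 0.04 × 0.03279 = 0.00131.
- SE (a = 0) = √(0.00539/6) = 0.02998, and 0.0752/0.02998 = 2.509.
- One-sided: Φ(2.509 − 1.645) = 80.6%. Two-sided: Φ(2.509 − 1.960) = 70.8%. Two-sided with a = 1: 62.9%.

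Of the variants tried, only the one-sided, uncorrected one uses every stated input and returns about 80%. It does so with the full 16% as the control rate. The others that come near 80% need the loss to follow-up reduced or removed, or the clustering dropped. Starting from 12% instead, over three years with 20% loss, power is 72.5% one-sided (a = 0), and 61.1% (a = 0) or 53.4% (a = 1) two-sided. The protocol does not settle sidedness: the variant that reproduces the HSV-2 figure gives a detectable HIV ratio of 0.24, not the stated 0.29.

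**Step 2: lower the control rate and keep the ratio at 0.53.** The reduction r is an assumption, because the protocol gives no figure. λ0 = 0.16(1 − r), λ1 = 0.53 λ0, a = 0, three years.

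| r | λ0 | λ1 | SE | (λ0 − λ1)/SE | Power, one-sided | Power, two-sided | Detectable ratio at 80%, one-sided |
|---|---|---|---|---|---|---|---|
| 0 | 0.160 | 0.0848 | 0.0300 | 2.509 | 80.6% | 70.8% | 0.534 |
| 10% | 0.144 | 0.0763 | 0.0281 | 2.409 | 77.8% | 67.3% | 0.517 |
| 20% | 0.128 | 0.0678 | 0.0262 | 2.300 | 74.4% | 63.3% | 0.498 |
| 30% | 0.112 | 0.0594 | 0.0242 | 2.180 | 70.4% | 58.7% | 0.474 |

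**Step 3: check whether the 22% identifies the rate.** Two-year cumulative incidence is 1 − e^(−0.32) = 27% to 1 − 0.84² = 29% at 16% a year. At 12% a year it is 1 − e^(−0.24) = 21% to 1 − 0.88² = 23%. The 22% therefore fits 12%, not 16%.

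**Step 4: two years instead of three.** The general design describes one year of intervention and one year after it, so y = 40. At 16%, one-sided, a = 0, power is 68.9% with r = 0, and 65.6%, 61.8% and 57.6% with r = 10%, 20% and 30%. The start is lower for a separate reason; the further loss from r is of similar size.

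**The case against.** *The figures describe a trial against no intervention.* A reader might infer this, but the text does not say it. The HSV-2 comparison is between arms, the HIV ratio is intervention to control, and the Aim 2 paragraph uses background for what works as the control-arm value. Only the HIV sentence ties the rate to the target communities, and no passage calls it untreated. The source of the 16% is not shown, so the services its population already had cannot be known. What stands is that no control-arm rate is stated and no allowance is made.

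*Power collapses.* Holding the combined arm at 0.53 × 16% while controls improve moves the ratio to 0.53/(1 − r) = 0.59, 0.66 and 0.76. Power then falls to 66%, 47% and 27% one-sided, or 54%, 35% and 18% two-sided. The protocol does not support that reading: 0.53 is a detectable ratio between arms, and 6.3% is roughly that ratio applied to 12%, not a rate the package is expected to reach.

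*The control effect may be small.* Background section G also says that the evaluations were done straight after the programme, that sustained change is undocumented, and that education alone is inadequate. This is a fair reason to expect a modest effect. It does not justify an unstated zero while the course, condoms and counselling are being delivered.

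*The 12% may already be a discounted control rate.* The protocol does not present it so, and step 3 suggests 12% is itself the background rate. Even at 12%, the stated inputs give 72.5% one-sided, not 80%.

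*Some shared items do not bear on HSV-2.* Agreed. Hormonal contraception matters for pregnancy, and the protocol gives Red Cross training no link to infection. The comparator is itemised under Procedures, so rewording it in the aims would be editorial.

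**Conclusion.** The point holds in moderate form. The stated 80% is reached, at best, with the full 16% background rate used as the control rate and a one-sided test without the small-cluster correction. With three years of follow-up and the stated loss and clustering, the two-sided figure before any control-arm effect is 53% to 71%, depending on whether 12% or 16% is used and whether the correction is applied. That shortfall comes from those choices, not from the control package.

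The package adds a further loss. For an assumed 10–30% lower control rate at an unchanged ratio of 0.53 and a 16% background, it is about 3 to 10 points one-sided and 3.5 to 12 points two-sided. The direction is firm. The size rests on the assumed 10–30%, for which the protocol gives no figure.

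For pregnancy no size can be computed, because no rate is given. Carrying over the HSV-2 calculation is unsupported when contraception is available to both arms.

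**What to change.** In section 1.a:
- State an assumed incidence for the life-skills control arm and its basis. Reconcile it with the 16%, 12% and 22% figures and with the two-year follow-up in the general design.
- State the detectable ratio as combined arm against control arm, with the sidedness of the test.
- Restate power over a range of control rates, for example 0–30% below background.
- Replace the sentence that carries the HSV-2 calculation over to pregnancy with a separate control-arm pregnancy rate that allows for contraception on request.

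The cost is a rewritten paragraph and a short recalculation. Main-study enrolment is already complete at 315, and nothing here changes sample size, visits or procedures. The one downside is a less favourable stated power.
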